#### Guided relaxation

The audio file and live sessions will have the following instructions for guided relaxation before meditation, rejuvenation, and before sleep. The audio duration will be six minutes:

1. Please sit comfortably and breathe normally. Gently close your eyes
2. Now, move your attention to your toes. Wiggle them a little and allow your toes to relax
3. Feel very relaxing energy entering your feet from the ground allowing your feet to relax. Let this energy slowly move up, relaxing your ankles, lower legs, calf muscles, knees, upper legs, and hips. Feel all these parts completely relaxed.
4. Allow this energy to slowly move up, relaxing your lower back and your upper back. Feel your entire back relaxed.
5. Slowly move your attention to your stomach area and allow all the muscles to relax.
6. Now, let the energy move up into your chest and let your chest deeply relax.
7. Move your attention onto your shoulders and feel as if they are melting away.
8. Let this energy slowly move into your upper arms, elbows, lower arms, hands, and fingers. Feel them completely relaxed.
9. Slowly move your attention to your neck and allow your neck muscles to relax
10. Gently loosen your jaw and allow your chin and all the facial muscles to relax. Your lips and your eyes are relaxing. Relax your forehead.
11. Gently move into your mind and allow your mind to relax deeply and completely. Relax the top of your head.
12. Gently scan your whole body from the top of your head to the tips of your toes and feel your entire body relaxed.
13. Now, gently move into your heart and settle in there. Rest your attention on the source of light that is already present within. Do this in a very gentle and natural way

#### Meditation practice

1. Participants will be asked to simply tune into their hearts and be open to any experience they may have as opposed to trying to visualize the light.

2. If their attention drifts, participants will be advised to redirect toward their hearts gently.
3. They will be asked to sit quietly for about 15-20 minutes by oneself or until the trainer says, "That is all."
4. They will be asked to spend 3-5 minutes after meditation to observe feelings and emotions and note them.

#### Rejuvenation practice

1. Sit comfortably and relax with the help of audio of guided relaxation.
2. Think that you are mentally letting go of all the complexities, heaviness, and emotional burdens from your system.
3. Settle down with the thought that the complexities, heaviness, and emotional burdens are going away.
4. Think that they are going out of your whole system, through your back, from the top of your head to your tailbone.
5. Mentally suggest that they are going out of your system from your back in the form of smoke or vapor.
6. It is an active yet gentle process. Do not dwell on specific events or things you want to get rid of. Simply brush them off.
7. Gently accelerate this process with confidence and faith, and apply your will as needed.
8. If your attention drifts, and you find yourself involved in other thoughts, gently bring your attention back to the rejuvenation process.
9. As the impressions are leaving from the back, you will start to feel lightness in your heart.
10. Once you feel lightness in your heart, think that a sacred current from the Source is entering into your heart from the filling the vacuum left by the outgoing impressions.
11. Do this for about 15 minutes.

#### Home practice:

- In the morning, the participants will be asked to listen to an audio file consisting of the Heartfulness relaxation technique followed by meditation for about 15-30 minutes in place of or in addition to guided sessions as per the convenience of the participants.
- In the evening or at the end of the day's work, the participants will be asked to listen to an audio file consisting of the Heartfulness relaxation technique followed by rejuvenation for about 15-20 minutes in place of or in addition to guided sessions as per the convenience of the participants.
- At night, participants were asked to listen to an audio file consisting of the Heartfulness relaxation technique for sleep. This was to be done in a supine position, and the instructions were similar to the morning meditation technique. This practice was suggested to be followed on a daily basis.

- Participants will be asked to self-report the adherence to the intervention at the end of the 6-week study period.

### Certified Heartfulness Trainers

[name] (PI) is a physician and a certified Heartfulness trainer who will provide education, training and conduct all virtual meditation sessions during this study.

If any unforeseen situation forces an absence of [name], Co-Primary investigator: [name] will start a Video meeting (without video interaction between participants and trainer) and invite one of the alternate Heartfulness trainers ([name], [name], [name]) to maintain the privacy of the participants.

### Gratitude practice group

All participants in the Gratitude practice group will be invited for an orientation session on the aspects of the study and review of the toolkit for cultivating the practice of gratitude in nursing. This program created by the American Nurses Foundation and the Greater Good Science Center (GGSC) at the University of California, Berkeley, is designed to support nurses' social and emotional wellbeing. This toolkit is based on scientific research revealing the many benefits of gratitude. This toolkit provides different ways for individuals to express gratitude during their daily interactions and work environment, such as writing a gratitude letter, taking a savoring walk, a few minutes before and after each patient encounter, during staff huddle, etc. Participants would have an opportunity to participate in a 21-days gratitude challenge by registering on [www.Thnx.org](http://www.Thnx.org) if offered during the study period. All participants will be sent an email once a week during the study period to provide a gentle reminder to practice gratitude. Participants will be asked to attend an orientation session via Zoom about Gratitude Science for 1 hour. If the participant cannot attend the meeting, they can review the recorded video for information. Participants will be provided with information to access podcast each week on gratitude practice during the 6-week study period. Tool kit available at: [https://ggsc.berkeley.edu/gratitudeforurses?\\_ga=2.59198189.1166833940.1621437217-1764624032.1620078854](https://ggsc.berkeley.edu/gratitudeforurses?_ga=2.59198189.1166833940.1621437217-1764624032.1620078854). Subjects in the control group will also complete the ProQOL-5 at the beginning and end of the six weeks and after 3 & 6 months unless they start practicing Heartfulness meditation.

### Data to be utilized

Participant Information from the Participant details form (attached)

Data from standardized assessment tools

From the Professional Quality of Life scale (attached)

From the Utrecht Work Engagement Scale (UWES)

Data will be extracted from the information collected from enrollment, assessment and classes and will be stored in a secured file only accessed by the PI.

Data analysis will include descriptive statistics, regression, and repeated measures ANOVA to assess the impact of any intervention on work engagement, compassion fatigue and burnout.

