### **The objectives of the study**

The primary objective of this study is to investigate an impact of a virtual, heart-based meditation program (Heartfulness practice) guided through a Heartfulness trainer compared with a self-motivated Gratitude practice for nurses designed by the American Nurses Foundation and the Greater Good Science Center (GGSC) at the University of California, Berkeley on the burden of compassion fatigue and burnout among the nurses and allied healthcare providers.

The secondary objective is to investigate if a virtual, Heartfulness practice guided through a Heartfulness trainer results in a sustained reduction in compassion fatigue and burnout as well as improvement in work engagement among the healthcare providers.

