### **Study Population and Recruitment Methods**

We would like to implement an adaptive recruitment strategy to recruit a higher number of participants in the intervention group expecting a high attrition rate observed in previous studies where meditation practice was employed as an intervention. We would like to recruit 200 participants in the intervention group and 100 participants in the control group. Willing volunteers will be consented to, enrolled, and data will be collected and analyzed.

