### **Study design**

This study will be randomized control trial where the participants will be randomly assigned to the Heartfulness meditation group (Intervention group) or the Gratitude practice group (Control group). All participants will be requested to fill out professional quality of life (ProQOL) survey and the “Participants’ Details” (including age, gender, work designation, years of experience, level of education, primary patient population etc.) forms before randomization. Participants will be subjected to computerized randomization to intervention group or Heartfulness meditation group and control group or the Gratitude practice group. All participants were requested to complete the professional quality of life (ProQOL) and , Work engagement scale at the baseline and at the end of 6-weeks, which will complete the first phase of the study.

If equal or more than 20 participants are willing to participate, we will continue with a second phase of the study where the trainer guided Heartfulness program will continue for six months to assess the long-term impact of Heartfulness practice on compassion fatigue and burnout. Email communication will be sent to all participants at the end of 6 weeks, asking for voluntary participation. Participants who volunteer for the second phase of the study will be asked to complete a same survey at three months and six months. Participants in Gratitude practice group will also be asked to complete the survey at three and six months after completion of study.

All participants in both groups will be provided with information, including recorded video presentations for Heartfulness meditation practice and the Gratitude practice, at the end of 6 weeks.

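### At 6 weeks, repeated measures ANOVA amounts to a change-score test in completers: less precise than adjusting for baseline, and at risk of bias under the attrition the protocol expects

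*Protocol*

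**What the plan says.** The primary objective compares Heartfulness with Gratitude "on the burden of compassion fatigue and burnout among the nurses and allied healthcare providers" (Protocol, The objectives of the study). Under Study design, the ProQOL and the work engagement scale are requested of all participants "at the baseline and at the end of 6-weeks, which will complete the first phase of the study".

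Under Study Population and Recruitment Methods, the investigators plan unequal recruitment, "expecting a high attrition rate observed in previous studies where meditation practice was employed as an intervention". Their response is: "We would like to recruit 200 participants in the intervention group and 100 participants in the control group".

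The analysis statement, under Data to be utilized, is a single sentence: "Data analysis will include descriptive statistics, regression, and repeated measures ANOVA to assess the impact of any intervention" on the listed outcomes. It names no method as primary and does not say what the regression would adjust for.

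Later follow-up is selective in both arms. In Study design: "Participants who volunteer for the second phase of the study will be asked to complete a same survey at three months and six months". In the Gratitude practice group section, controls complete the ProQOL "after 3 & 6 months unless they start practicing Heartfulness meditation".

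**The concern.** The protocol predicts loss in the meditation arm, and the only longitudinal method it names uses, in its classical form, only people with every wave entered. For the 6-week question those waves are baseline and 6 weeks. The group-by-time test then compares mean change between arms among completers.

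Two things follow. First, a change score gives the baseline a fixed weight of 1 instead of the weight its correlation with the outcome supports, so precision is lost. Second, if the people who leave Heartfulness differ at baseline from those who stay, the retained arms no longer start level. Regression to the mean then shows up as a difference in change. More recruits to Heartfulness bring more people through the same filter. That protects the count and leaves the imbalance as it was. At stake is whether a modest 6-week difference on the primary outcome reflects the practice or who stayed.

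**Working it through.** **The plan's own figure.** The 200 and 100 come without alpha, power, effect size, SD or dropout rate, so there is no calculation to reproduce. Correlations, dropout rates and dropout mechanisms below are assumptions, shown over a range. Scores are in units of one SD, taken as equal at both waves; higher means more burnout.

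**Precision.** Let r be the correlation between baseline and 6-week score.

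- Change score: variance per person 2(1 − r).
- ANCOVA: variance per person 1 − r².
- Ratio: (1 − r²) / [2(1 − r)] = (1 + r)/2.

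| r | ANCOVA variance / change-score variance |
|---|---|
| 0.5 | 0.75 |
| 0.6 | 0.80 |
| 0.7 | 0.85 |

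As an illustration, assume 50% Heartfulness and 10% Gratitude dropout (100 and 90 completers), a true difference of 0.35 SD and two-sided alpha 0.05. At r = 0.5 the standard errors are √[1.00 × (1/100 + 1/90)] = 0.145 for change and √[0.75 × (1/100 + 1/90)] = 0.126 for ANCOVA. Power is 67% against 79%. At r = 0.7 it is 88% against 92%.

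**Bias when dropout depends on baseline.** Suppose no true effect, and let m be the mean baseline score among those retained in an arm. Their expected 6-week score is r·m, so their expected change is −(1 − r)·m. The false difference in change between arms is therefore −(1 − r)(m_H − m_G). With log-odds of dropout rising by 1 per SD of baseline (odds × 2.7), numerical integration over a standard normal baseline gives m = −0.413 at 50% dropout and −0.173 at 20%.

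| r | Gratitude dropout 0%: (1 − r) × 0.413 | Gratitude dropout 20%, same mechanism: (1 − r) × 0.240 |
|---|---|---|
| 0.5 | 0.21 SD | 0.12 SD |
| 0.6 | 0.17 SD | 0.10 SD |
| 0.7 | 0.12 SD | 0.07 SD |

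Here the more burned-out leave, and the error runs against Heartfulness; if the less burned-out leave, it reverses. ANCOVA has bias of about 0 in this setting, because the comparison is made at equal baseline. With a log-odds of 0.5 per SD, 20% Gratitude dropout and r = 0.6, the change-score bias is 0.06 SD. Under completely random dropout it is 0 for both methods.

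**Bias when dropout depends on the 6-week score.** With 50% Heartfulness dropout, log-odds 1 per SD of the 6-week score, no Gratitude dropout and r = 0.6, simulation gives a bias of 0.27 SD for ANCOVA and 0.17 SD for change. With 30 to 50% Heartfulness dropout, 10% Gratitude dropout unrelated to score, log-odds 0.5 or 1, and r = 0.5 or 0.7, the ranges are 0.07 to 0.32 SD for ANCOVA and 0.04 to 0.21 SD for change. These errors favour Heartfulness when those with high 6-week burnout leave.

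**What over-recruitment does.** 200 × 0.5 = 100 Heartfulness completers, equal to the control target. The sample size does not appear in the bias formula, so the bias stays.

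**The case against.** **Much of this is silence that a statistical analysis plan may fill.** The analysis set, missing-data method and covariates are commonly fixed there, and regression, which the protocol also lists, could be baseline-adjusted. This stands in part: the protocol does not establish that ANOVA is the sole or primary analysis. What remains is that it names ANOVA as a means of assessing impact, in a trial for which it predicts high attrition.

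**The size depends on the scenario.** No dropout rate, mechanism or correlation is in the protocol, and dropout of the same kind in the control arm shrinks the bias. This stands. A reader might infer that the primary comparison is biased; the documents support only a risk.

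**Baseline adjustment is no cure.** This stands too. If dropout follows the 6-week score, ANCOVA does worse than change scores. A mixed model with baseline as covariate does not rescue it: with one follow-up wave, anyone without a 6-week score contributes nothing, and the model reduces to ANCOVA in completers.

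**Stronger readings that the documents do not support:**

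- *A four-wave ANOVA would reduce the 6-week comparison to phase 2 volunteers, perhaps 20 of 200.* Study design says baseline and 6 weeks complete the first phase. The 20 is the threshold for starting the second phase, not a forecast of the analysed sample.
- *People who stop attending are not surveyed at 6 weeks.* Study design requests that survey of all participants.
- *The allocation should be 1:1.* The variance of 200:100 relative to 150:150 is 1.125 with equal retention, but 1.05 at 60% against 90% and 1.04 at 50% against 80%. Under the differential retention the protocol expects, the cost is small and the choice is a trade-off.

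**Conclusion.** The point holds as a weakness in the named analysis. The loss of precision is algebraic for the two-wave group-by-time test: the ANCOVA variance is 0.75 to 0.85 of the change-score variance at assumed r = 0.5 to 0.7, using data already collected. The bias is conditional. It needs dropout that differs by arm and depends on baseline; it is then about 0.07 to 0.21 SD under 50% Heartfulness dropout, log-odds 1 per SD, 0 to 20% Gratitude dropout and r = 0.5 to 0.7. Weaker dependence gives less. ANCOVA's near-zero bias in that setting rests on a linear relation with baseline that is the same in both arms. For dropout that depends on the unseen outcome, neither method is safe.

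**What to change.** In Data to be utilized, name one primary analysis: ANCOVA of the 6-week ProQOL scores that carry the primary objective, with baseline score as covariate, by randomised arm. Include everyone with a 6-week survey, regardless of session attendance.

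Keep the 3- and 6-month data in a separate, secondary mixed model, reported with the caveat that follow-up there is selective in both arms.

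Add a delta-adjusted sensitivity analysis: impute missing 6-week scores from baseline and arm, shift the imputed values over a range fixed in advance, separately by arm, and report the shift at which the conclusion changes. This addresses the mechanism that baseline adjustment leaves open.

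The cost is revised wording and a little more analysis work with standard software. No extra participants or assessments are needed, and the recruitment target can stay as it is.

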### **Risks and Risk Management**

For Heartfulness Meditation: Some participants may have limited endurance and decreased strength related to their health conditions. Some may also have concurrent medical problems such as arthritis or other challenges. Participants receive written and verbal instructions to never do anything that they feel is dangerous or painful to them.

In the practice of meditation, although calmness is induced, there can also be the experience of unwanted emotions and thoughts arising and passing. There may also be bodily discomfort through sitting for a prolonged period. If the participant is unable to continue meditation due to this, they may open their eyes briefly, take a slow deep breath, and then close their eyes to continue to meditate, or alternatively, they may leave if that is their desire.

The recognition of this is part of the long-term benefit of the course, but it can be upsetting or uncomfortable in the short term. To address this, participants may change their posture to continue meditation. Participants have their first experience of the technique in the supportive atmosphere of the virtual classroom and are taught what to expect and how to cope with experience as it unfolds. They also have contact information from the trainer, and participants may call or email the trainer with any questions or concerns. If any experience in class reveals intent to self-harm, the investigators will follow up promptly, and participants will be advised to contact emergency room or primary care physician.

For the Gratitude Science education, there is minimal risk. The education program is freely available on the web.

As for both interventions, Participants often share their experiences in the group setting; therefore, confidentiality applies to trainers, educators, and group members. At the first Heartfulness Medication class, participants sign an agreement that they will hold class events confidentially and not give each other advice.

### **Benefits to Subjects**

Participants who complete the course either in the Heartfulness meditation group or the Gratitude practice group may experience reduced compassion fatigue and burnout and may have an improved sense of emotional wellness and improvement in the quality of sleep.

### **Compensation/Incentives and Research-related Costs**

There will be no compensation, incentive, or research-related costs to the participants associated with the study.

### **Alternatives/Choice to Participants**

Subjects may choose not to participate in this project with no effect on their current situation. Participants may also choose to withdraw from the program at any time with no consequences. There is no fee/charge for either program.

### **Research Materials, Records and Confidentiality**

All information will be drawn from the assessment tools previously described. Medical records will not be utilized in this project. Data will be reported in aggregate so that no individual health information is revealed.

Identifiable information will be gathered initially then replaced by a survey identification number to protect each participant's identity. Other assessment forms will be identifiable by survey identification number.

All collected data will be stored on a secure password-protected file on Wright State University provided secured Proofpoint Secure Share.

### **Intended Use of Research**

The investigators plan to present study results in a poster format at conferences related to medical research and evidence-based practice and present to any relevant medical committees. The investigators will disseminate the findings at professional conferences and through publication. One or both programs may demonstrate a benefit for healthcare organizations.

